## Abstract

**Background:**

Textile industry has been widely implicated in environmental pollution. The health effects of residing near manufacturing industries are not well documented in India, especially in central India. Hence, a cross-sectional environmental monitoring and health assessment study was initiated as per directions of the local authorities.

**Methods:**

Comprehensive exposure data about the concentrations of relevant pollutants in the ambient air and ground water samples in the study area will be collected over one year. Using stratified random sampling, 3003 apparently healthy adults will be selected from the study area. Sociodemographic and anthropometric information, relevant medical and family history, and investigations including spirometry, electrocardiogram, neurobehavioral tests, and laboratory investigations (complete blood count, lipid profile and random blood glucose) will be conducted. Finally Iodine azide test and heavy metal level detection in urine and blood samples respectively will be conducted in a subset of selected participants to assess individual pollution exposure. Ethics approval has been obtained from the Institutional Ethics Committee of the National Institute for Research in Environmental Health (No: NIREH/IEC-7-II/1027, dated 07/01/2021).

**Discussion:**

This manuscript describes the protocol for a multi-disciplinary study that aims to conduct environmental monitoring and health assessment in residential areas near viscose rayon and associated chemical manufacturing industries. Although India is the second largest manufacturer of rayon, next only to China, and viscose rayon manufacturing has been documented to be a source of multiple toxic pollutants, there is a lack of comprehensive information about the health effects of residing near such manufacturing units in India. Therefore implementing this study protocol will aid in filling in this knowledge gap.

## Introduction

Industrial development has contributed to economic growth but at the same time industrial activities constitute a major source of environmental pollution [1]. Adverse health effects posed by industrial pollution is well-established [1]. De Sario et al., 2018 [2] in their scoping review identified 762 epidemiological studies which conclude that living in industrial areas is associated with a wide range of diseases ranging from malignancies and respiratory diseases to adverse birth outcomes and even premature mortality. Of these studies, few were conducted in India that focussed on the public health and environmental effects of industrial emission. Chatham-Stephens et al., 2013 [3] using the Toxic Sites Identification Program developed by the Blacksmith Institute and the United Nations Industrial Development Organization identified 221 point-sources of pollution from industrial activities in India that pose risk to public health. The authors [3] calculated that exposure to pollutants generated in industrial regions in developing countries like India, Indonesia, and the Philippines pose equal or even greater risk to human health than widespread communicable diseases like malaria and account for almost eight million years of healthy life lost due to disease, disability or premature death (i.e. 828,722 Disability-adjusted Life Years) among the 8.6 million exposed population in the three countries. Therefore, research is needed to assess the environmental health effects of major industries in India.

India, being a rapidly developing economy, is home to multiple industries. Textile industry, plays a critical role in Indian economy as it is the second largest source of employment for a country which is counted amongst the top producers, exporters as well as consumers of textiles in the world [4]. However, the textile industry has been widely implicated in pollution of various environmental matrices like air, water and soil both in India [5, 6] and other countries [7, 8]. It accounts for almost twenty percent of global industrial activity induced water pollution [7] and is associated with emission of many gaseous pollutants into ambient air [9]. Multiple studies [10. 11] have documented the adverse health effects of exposure to the chemical pollutants that emanate from textile and associated chemical manufacturing. In India, research [12–14] on the health effects of such textile industry has mostly been focussed on individuals who are occupationally exposed to the chemical pollutants. The health effects of residing near manufacturing industries are not as well documented.

The industrial area of Birlagram Nagda in the central Indian state of Madhya Pradesh (MP), has been under scrutiny due to the pollution emanating from the multiple viscose rayon textile and associated chemical manufacturing industries operating in the area [15]. As per data compiled by the Central Pollution Control Board (CPCB) [16] in 2013, the apex government run agency monitoring environmental pollutant concentrations in the country, the area has a comprehensive environment pollution index score of 66.67, which indicates that it is among the “severely polluted” industrial clusters in India. Although recent statistics have shown improvement in the area’s pollution index, it is still listed in the top hundred polluted industrial clusters in India [17]. Major chemical pollution associated with viscose rayon textile manufacturing occur secondary to gaseous emission of carbon disulphide (CS_2_), Hydrogen Disulphide (H_2_S), Hydrogen Chloride (HCl), Chlorine (Cl_2_), Sulphur oxides (SO_2_ and SO_3_) and untreated discharge of viscose fibre wastewater effluent containing high concentration of heavy metals, and other toxic substances into natural water sources [9]. However, there is hardly any scientific evidence regarding the health effects of residing near the industries of Birlagram. Considering the growing health concerns of the local public, regulatory authorities in India directed the industries operational in the region to implement pollution control strategies as well as commissioned detailed environmental and health-oriented investigation of the issue [18]. The current study was initiated as per directions of the local authorities to evaluate the health effects of exposure to multiple pollutants emitted from the industrial activity in Birlagram. Specifically, the objectives of the current study include:

To measure the concentration of gaseous pollutants (i.e. CS_2_, H_2_S, HCl, Cl_2_, and SO_2_) in the ambient air in the study area.To measure the concentrations of heavy metals and anions [i.e. lead (Pb), mercury(Hg), aluminium (Al), chloride (Cl^-^) and sulphate(SO_4_^2-^)] in groundwater samples.To determine the association between the concentration levels of pollutants in air and water samples with that in bio-samples (blood and urine).To identify the association between exposure to pollutants and health effects in study participants.

## Methods and analysis

### Study design

This is the protocol for a cross-sectional research study that aims to collect and correlate comprehensive exposure and health outcome information to ascertain objective achievement (see Fig 1). This study will be conducted during a duration of one year. The time schedule of various study methods of this protocol is described in Fig 2.

**Fig 1 pone.0264154.g001:**
[figure not shown]
Graphical abstract: Overview of the study methodology. [Note: carbon disulphide (CS_2_), Hydrogen sulphide (H_2_S), Hydrogen Chloride (HCl), Chlorine (Cl_2_), Sulphur oxides (SO_2_), lead (Pb), mercury(Hg), aluminium (Al), chloride (Cl^-^), sulphate (SO_4_^2-^), body mass index (BMI), Electrocardiogram (ECG), Pulmonary function test (PFT), Random Blood glucose (RBG), Complete blood count (CBC)] (The graphical abstract image has been created by the research team using copyright-free images of Indian map and industry from https://pixabay.com).

**Fig 2 pone.0264154.g002:**
[figure not shown]
Time schedule of activities. [Note: Each numbered column represents one month of the project duration with the total duration of the project being 12 months].

### Setting

This study will be conducted in and around the Birlagram industrial region located in Nagda city in the Ujjain district (administrative unit) in the central Indian state of MP. Almost 72 million individuals reside in MP, most (72%) of whom reside in rural areas and depend on agriculture for their livelihood [19]. However, industrial activity in MP is gradually increasing [20] and multiple large scale industries in the Ujjain district [21] constitute an emerging public health concern for the province that needs to be evaluated.

The Birlagram industrial area is situated within the borders of Nagda city which in turn is surrounded on all sides by villages [15]. The industries situated in Birlagram are directly or indirectly (through production of chemical raw materials) involved in synthetic textile (viscose rayon) manufacturing [22]. Including the population residing in Birlagram itself, Nagda city has a total population of more than 0.1 million. River Chambal is the main source of water for the region and previous research findings highlight the poor quality of its water [23]. Details on air quality of the area are lacking in published literature.

### Participant selection and sampling strategy

#### Sample size calculation

As the health effects of residing near textile manufacturing industries in Birlagram, India are not previously documented, we calculated the sample size using the statistics reported by a previous study conducted in Taiwan where authors [24] found that 26.3% of the population exposed to emissions from a viscose rayon manufacturing industry had electrocardiogram (ECG) abnormalities. Since one of our outcomes is the identification of the proportion of exposed population in Birlagram, India with ECG abnormalities, we calculated sample size as follows:

$$\text{Sample}\;\text{size}\;\left(\text{n}\right)=\frac{{\text{z}}^{2}\text{pq}*\left(1+\text{R}\right)*\text{Deff}}{{\text{d}}^{2}}$$

Where, p = Expected population proportion = 0.26; q = 1-p = 0.74; z = z value for 5% level of significance is 1.96; R = Non-response rate (assumed to be 30% as pooled non-response rate reported by a systematic review of participation response in Indian industrial surveys [25]); Deff = Design effect(1.25 for systematic sampling); and d = Margin of error 2% (assumed to be 0.02). The calculated sample size was 3003.

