**Fig 3 pone.0264154.g003:**
[figure not shown]
Map of the study area created by research team to assist in selection of exposure monitoring locations and in participant sampling. [Note: The inset in the map shows the Ujjain district of the central Indian province of MP. Within the Khachrod Tehsil of the Ujjain district, lies the study area of the current project. Considering the Birlagram industrial region as the centre, three concentric circular regions were demarcated based on distance (2, 5 and 10 km from the centre)].

Finally, 2000 participants will be selected from the villages in the northern hemisphere while 1003 will be taken from the villages in the southern hemisphere within the 10km radius comprising a total of 3003 participants. In each hemisphere, a fixed number of villages will be selected randomly from those situated in each of the 0-2km, 2-5km and 5-10km zones. Further in each selected village, using the list of all individuals residing in the villages that will be retrieved from the local authorities as the sampling frame, individuals meeting the eligibility criteria will be randomly invited for participation in the study. Total number of individuals sampled in each village will be proportionate to the total population of the selected village.

Participants will be selected for the study only if they fulfill all the following criteria:

Adults (≥18 years of age) of both genders (except pregnant women),Should have been residing for at least one year in the selected village,No history of neuropsychiatric conditions that might hinder completion of neurobehavioral tests,No history of other conditions that are contraindications for performing Pulmonary function test (PFT) like presence of any active disease (e.g. pulmonary Tuberculosis, active haemoptysis, orofacial pain, acute respiratory infection including COVID-19 i.e. coronavirus disease caused by SARS-Cov-2 virus) or recent history (within previous 1 month) of myocardial infarction/aneurysm/surgery, etc.

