#### Data management and analysis

All participants’ data will be coded by assigning unique identifiers. These codes will be used to identify and link various parameters of the individual participants. Data from the filled questionnaires/clinical proforma as well as the laboratory analysis values will be entered into the latest version of Microsoft Excel spreadsheets. Statistician of the team will supervise data entry and to ensure error-free data at least 10% of the entered data will be randomly verified.

Once data entry is complete, hard copies of questionnaire/proforma will be stored in a secure archive in the institute. Similarly, all entered data will be stored in password protected computer systems with access restricted to the research team alone. The data collected/generated in this study will be stored for a period of ten years. The primary investigator will be in-charge of data safety and back-up maintenance. Anonymized data set will be shared publicly during publication of study results.

All statistical analyses will be performed using IBM SPSS Statistics (version 25). For ordinal and continuous variables, the values will be given as descriptive statistics (like mean, median, standard deviation, 95% confidence interval, interquartile range); and categorical variables will be given as numbers (percentages) and proportions. Association for different health aspects with pollution level of various parameters of air/water will be made using Pearson’s chi-square test for independent categorical data. By considering the variability within and between groups; t-test and ANOVA will be used to analyze the mean differences between two and more groups respectively for various anthropological parameters, the concentration of air/water pollutants, etc. The Mann–Whitney U test and Wilcoxon signed ranks test will be used for independent and dependent for ordinal and continuous data with respect to different health aspects. Pearson and Spearman’s correlation coefficient will be used to examine the association between different variables. Multiple linear and logistic regression models will be used to estimate the relationship for different neurological assessments with a set of the independent variable. For all statistical tests, two-sided P-values <0.05 will be considered to be significant.

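### The assumed 30% non-response is met only by enlarging the sample, so the ECG prevalence that sizes the study, reported as a plain percentage, is open to non-response bias

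*Protocol article*

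**What the plan says.** All references are to the protocol article.

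- **Sample size calculation.** The study is sized to estimate the proportion of the exposed population with ECG abnormalities. The inputs are "p = Expected population proportion = 0.26; q = 1-p = 0.74", "z = z value for 5% level of significance is 1.96", "Deff = Design effect(1.25 for systematic sampling" and "d = Margin of error 2% (assumed to be 0.02". Non-response enters as "R = Non-response rate (assumed to be 30% as pooled non-response rate reported by a systematic review" and is handled by the factor (1+R). The result: "The calculated sample size was 3003". Non-response is mentioned nowhere else in the article.
- **Sampling strategy.** Eligible people are invited at random, "using the list of all individuals residing in the villages that will be retrieved from the local authorities as the sampling frame". No record or comparison of those who decline is described.
- **Data management and analysis.** On reporting: "categorical variables will be given as numbers (percentages) and proportions". The section goes on to name tests, correlations and regressions, but no weighting or adjustment for response.
- **Discussion.** The stated limitations are the lack of follow-up, recall bias and residual confounding. Non-response is not among them.

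**The concern.** On the plan's own assumption, 3 in 10 invited people provide no ECG. A larger sample makes up for the lost numbers. It does not make those who came resemble those who did not. A plain percentage among participants estimates the population proportion only if prevalence is the same in both groups, or if the difference is adjusted for.

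The setting gives some reason to ask. The Introduction refers to public concern about health, the Discussion to a continuing dispute among residents, manufacturers and authorities, and Ethics and dissemination to individual health reports for participants. Any of these could affect who accepts an invitation, and so could age and sex. The documents do not say in which direction.

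At stake is the precision target itself. A bias moves the estimate without widening its interval, so a nominal 2-point margin could be reported around a shifted value.

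**Working it through.** **1. The plan's own figure.** n = z²·p·q·(1+R)·Deff/d² = 1.96² × 0.26 × 0.74 × 1.30 × 1.25 / 0.02² = 3002.69, rounded up to 3003. This reproduces the article. Without the factor 1.30, n = 2309.76, or 2310, with a half-width of 2.00 points.

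**2. Bias.** For a percentage among responders, bias = R × (responder prevalence − non-responder prevalence), with R = 0.30. Sample size does not appear in it. The gap that equals the margin is 0.02/0.30 = 6.7 points. For example, 26.0% in responders and 19.3% in non-responders gives a true 0.70 × 26.0 + 0.30 × 19.3 = 24.0%. The gap is an assumption, so a range is shown.

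**3. Effect on the interval.** With SE = 0.02/1.96, coverage of the nominal 95% interval is Φ(1.96 − bias/SE) − Φ(−1.96 − bias/SE):

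| Assumed gap (points) | Bias (points) | Coverage |
|---|---|---|
| 3 | 0.9 | 86% |
| 6.7 | 2.0 | 50% |
| 10 | 3.0 | 16% |

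The article does not say whether 3003 are invited or examined. If 3003 are invited and 70% respond, 2102 remain, the half-width is 1.96 × √(0.26 × 0.74 × 1.25/2102) = 2.10 points, and a 2.0-point bias gives 54% coverage. If 3003 are examined, the half-width is 1.75 points and coverage is 39%. For a given bias, the larger sample covers worse.

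**4. How much age and sex alone could do.** All inputs here are assumed. Population shares are 0.30 younger men, 0.20 older men, 0.30 younger women and 0.20 older women. Prevalence is 16% under 45 and 41% at 45 or over, so overall 0.60 × 16 + 0.40 × 41 = 26%. Response rates are listed in the same order. The Kish factor for weighting back to the population is (Σ share × rate) × (Σ share/rate).

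- Rates 60, 75, 70, 80%: overall response 0.18 + 0.15 + 0.21 + 0.16 = 0.70. Responder prevalence (0.16 × 0.39 + 0.41 × 0.31)/0.70 = 27.1%, a shift of +1.1 points. Kish factor 0.70 × (0.500 + 0.267 + 0.429 + 0.250) = 1.01.
- Rates 50, 80, 75, 85%: overall response 0.15 + 0.16 + 0.225 + 0.17 = 0.705. Responder prevalence (0.16 × 0.375 + 0.41 × 0.33)/0.705 = 27.7%, a shift of +1.7 points. Kish factor 0.705 × (0.600 + 0.250 + 0.400 + 0.235) = 1.05.

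These are illustrations, not bounds. Rates of 50, 85, 70, 85% give (0.16 × 0.36 + 0.41 × 0.34)/0.70 = 28.1%, or +2.1 points. In each case weighting to the true age-sex totals restores 26%, because response was assumed to depend on nothing else.

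**The case against.** The strongest case against is that this is an omission from a condensed article. Inflating for non-response is ordinary planning, the reporting sentence is generic and does not exclude weights, and adjustment could sit in a full protocol or analysis plan that is not shown. The bias also needs a responder gap for which the documents give no figure. The 30% is itself a planning assumption from surveys elsewhere. A local dispute could move response either way, and many people would not know of an ECG abnormality before being tested.

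Much of this stands. The bias is possible, not demonstrated, and the reporting sentence is silent on weights rather than opposed to them. But the article does set out the sizing target, its answer to non-response and its analysis methods. Following them as written leaves the sizing proportion open to uneven response by age and sex. An analysis plan could add weights later, but it could not recover the village, age and sex of decliners if fieldwork had not recorded them.

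Two objections limit the remedy, and both are right. Weighting on age, sex and village cannot remove selection on abnormality or on concern within those groups. The lists cannot give totals of eligible adults either, because eligibility depends on length of residence, pregnancy and medical history, which nothing suggests they hold.

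A reader might also infer that the zone comparisons are distorted. If 80% of people with abnormalities and 66.5% of others responded near the plants, a true 26% would appear as 0.208/(0.208 + 0.492) = 29.7%, an odds ratio of 1.20 against a zone with unselective response. This is an upper illustration. It requires response to depend on the abnormality itself and to differ by zone, which the documents do not support, and the weighting proposed here would not correct it. It forms no part of the case.

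**Conclusion.** The point holds in a limited form. The plan recognises substantial non-response and answers it only with sample size, which leaves the reported ECG prevalence unprotected against bias. The possible size is 0.30 times an unknown gap: 0.9 points for a gap of 3, the full 2-point margin for 6.7, and 3.0 points for 10. Under the assumed age-sex patterns the shift is about 1 to 1.7 points, which is material against a 2-point margin.

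A reader might go further and conclude that the prevalences will be biased, or that the interval will in fact cover only half the time. The documents do not support that. The gaps, prevalences by age and response rates above are all assumptions, and with no gap there is no bias. The conclusion does not depend on whether 3003 means invited or examined, and it is separate from the choice between (1+R) and 1/(1−R) as the inflation factor. It is worth changing because a standard and better estimator is available from a list the study will already hold.

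**What to change.** In Data management and analysis, state that the ECG and other population prevalences will be weighted, by post-stratification or raking, to the adult age-sex-village totals of the resident lists named under Sampling strategy, with unweighted figures alongside. This assumes that the lists show age and sex, which should be confirmed.

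In the field procedures:
- log the outcome of each invitation (examined, refused, not found, ineligible) by village, age band and sex;
- report response by zone and hemisphere.

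Beside the 2-point margin, show a sensitivity range for stated responder/non-responder gaps, such as 3, 6.7 and 10 points. Add non-response to the limitations. State that weighting removes only the part explained by age, sex and village, and that list totals only approximate the eligible population.

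The cost is some analysis wording and an invitation log kept from the start of fieldwork, with no additional participants or examinations. The statistical downside is a variance increase of roughly 1 to 5% in the illustration.

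### The sample size multiplies by (1+R) to cover 30% non-response; the factor that preserves the required number is 1/(1-R), and what 3003 counts is left open

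*Protocol article*

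**What the plan says.** Under Sample size calculation, the Protocol article sizes the study to estimate the proportion of exposed residents with ECG abnormalities. The printed formula is n = z²pq(1+R)Deff/d². Its inputs are given as:

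- for the proportion, "p = Expected population proportion = 0.26; q = 1-p = 0.74", taken from a study in Taiwan in which "26.3% of the population exposed to emissions from a viscose rayon manufacturing industry had electrocardiogram (ECG) abnormalities";
- the usual two-sided 5% normal quantile, 1.96, for z;
- for the allowance for people who do not take part, "R = Non-response rate (assumed to be 30% as pooled non-response rate reported by a systematic review";
- for the sampling design, "Deff = Design effect(1.25 for systematic sampling";
- for the precision sought, "d = Margin of error 2% (assumed to be 0.02".

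The result is "The calculated sample size was 3003". Under Sampling strategy the same figure is split into 2000 people from the northern half and 1003 from the southern half, "comprising a total of 3003 participants". That section also says that eligible people are invited at random from village lists. The Methods paragraph of the Abstract describes the 3003 as adults to be selected. The article gives no separate number of people to approach.

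**The concern.** If a fraction R of those approached does not respond, N people approached give N(1-R) responders. To end with n responders, N must equal n/(1-R). Multiplying n by (1+R) falls short: with R = 0.30, 1.30 × 0.70 = 0.91, so 9% of the required number is lost by construction.

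The article also does not say what 3003 counts. As a figure already enlarged for non-response, it would be a number to approach. As a number of participants, it would be a number who take part. The precision that can be claimed for the ECG proportion differs between the two, and 3003 is the only total in the article. It sets the 2000/1003 split and the numbers drawn per village.

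**Working it through.** **Inputs**, all from Sample size calculation: p = 0.26, q = 0.74, z = 1.96, R = 0.30, Deff = 1.25, d = 0.02. Deff is taken as printed.

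**1. Reproduce the plan's figure.**
- Base: z²pq/d² = 3.8416 × 0.1924 / 0.0004 = 1847.8
- With design effect: 1847.8 × 1.25 = 2309.8, so 2310 responders are needed
- With the printed factor: 2309.8 × 1.30 = 3002.7, rounded up to **3003**

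This matches exactly and confirms that (1+R) was the factor used. The unrounded source proportion, p = 0.263, would have given 3025.

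**2. Inflate with 1/(1-R).**
- 2309.8 / 0.70 = 3299.7, so **3300** to approach
- Difference from the printed figure: 3300 - 3003 = 297, or 297/3003 = 9.9%

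**3. If 3003 is the number approached.**
- Responders: 3003 × 0.70 = 2102
- Shortfall: 2310 - 2102 = 208, or 208/2310 = 9.0%
- Margin: 1.96 × √(1.25 × 0.1924 / 2102) = 0.02097, about **±2.10%** (also 2.10% at p = 0.263)
- Non-response at which 3003 approached would still give 2310: 1 - 2310/3003 = 23.1%, below the 30% assumed

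**4. If 3003 is the number who take part.**
- Margin: 1.96 × √(1.25 × 0.1924 / 3003) = 0.01754, about **±1.75%**
- Surplus over the requirement: 3003 - 2310 = 693

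| Reading of 3003 | Number analysed | Margin (plan: ±2.00%) |
|---|---|---|
| Approached, 30% do not respond | 2102 | ±2.10% |
| Take part | 3003 | ±1.75% |

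Under neither reading do 3003, R = 30% and a 2% margin all agree.

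**The case against.** The strongest reply is that nowhere does the article say that 3003 people are invited. It calls them participants and selected adults, and it applies the eligibility criteria at selection. Under Health assessment, the data are to come from everyone selected. Read literally, 3003 is the number with data, and the 2% target is met with room to spare. Setting an enlarged figure as the recruitment target and calling those people participants is also common practice.

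This stands as far as the consequence goes. A reader might infer that the study will miss its 2% margin, or that the two uses of 3003 contradict each other. The article supports neither. The missed margin depends on reading 3003 as the number approached, and the text is ambiguous rather than contradictory.

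Two further replies have weight. How many invitations go out, and whether non-responders are replaced, is field detail that a condensed article may leave to the full protocol. The one-in-ten blood subset under Human exposure assessment adjusts by itself to whatever number takes part. Neither is part of this point. The ECG proportion is also only one of the outcomes, and none of the four objectives in the Introduction is to estimate a prevalence, so 0.1 percentage point on one interval is minor.

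None of this rescues the factor itself. The formula, the definition of R, its value and the result are all printed, and (1+R) does not do what a non-response allowance is for.

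**Conclusion.** The point holds in a limited form. The printed formula is wrong for its stated purpose: on the plan's own inputs, 2310 responders at 30% non-response require 3300 people approached, not 3003. The effect on precision is conditional and small. At worst the margin is about ±2.10% on about 2102 responders instead of ±2.00%. If 3003 actually take part it is about ±1.75%, and the target is met.

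These figures assume the printed p, Deff and R. They concern the width of the interval only. It would be too strong to say that the error invalidates the study or that it is certain to fall short of its precision target. What needs correcting is the sample-size derivation and the meaning of its one total.

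**What to change.** In Sample size calculation, replace (1+R) with 1/(1-R), and state whether 3003 counts people approached or people enrolled. Then make the figures agree in one of these ways:

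- **Keep the 2% margin:** give 2310 as the number of responders needed and 3300 as the number to approach.
- **Keep 3003 as the number approached:** state about 2102 expected responders and a margin of about ±2.1%.
- **Keep 3003 as the number enrolled:** take R out of that number and state a margin of about ±1.75%.

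Use the same definition for the 2000/1003 split under Sampling strategy and for the Abstract. The second and third options cost one formula and a sentence or two, and need no extra participants. The first means approaching 297 more people than 3003, if 3003 was meant as the number approached.

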#### Sampling strategy

In this study stratified random sampling technique will be used for selection of participants where stratification will be done based on environmental factors that are likely to affect exposure. Since both distance from fixed contamination source as well as local environment features such as meteorology, topography, etc. are the major factors affecting the dispersion of both ambient air as well as water pollutants [26], a map of the study area was created to assist in selection of exposure monitoring locations and in participant sampling (see Fig 3). Briefly, taking Birlagram industrial region as the centre, villages located within consecutive circles of radius 2 kilometres (km), 5km and 10km were demarcated on the map using ArcInfo (version 10). This strategy was used as it is expected that gaseous pollutants’ dispersion occurs homogenously in all directions independent of anthropogenic roadways and that with increase in distance the pollutant concentration will become diluted enough to prevent adverse health effects [27]. Based on seasonal wind pattern data retrieved from local authorities, the north-eastern quadrant of the circular study area was seen to be the downwind area for most of the year. The downstream direction of River Chambal falls in the north-western quadrant of the circular study area. Therefore the majority of the pollutants are expected to disperse in the northern direction increasing the potential risk faced by the residents and so, we decided to over-represent the northern hemisphere.

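### The design effect of 1.25 is justified by systematic sampling, which the protocol does not use to select participants; for the two-stage village sample it describes, 3003 is likely to miss the ±2% margin unless within-village correlation is very small or many villages are drawn

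*Protocol article*

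**What the plan says.** Under Sample size calculation, the article sizes the study to estimate the proportion with ECG abnormalities. The inputs are "p = Expected population proportion = 0.26; q = 1-p = 0.74", "z = z value for 5% level of significance is 1.96", "d = Margin of error 2% (assumed to be 0.02)", "R = Non-response rate (assumed to be 30% as pooled non-response rate" and "Deff = Design effect(1.25 for systematic sampling)". The result is 3003.

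Under Sampling strategy, the design has a different name: "In this study stratified random sampling technique will be used for selection of participants". The text after Fig 3 gives the steps. Within each hemisphere, a fixed but unstated number of villages is drawn at random from each of three distance zones (0-2, 2-5 and 5-10 km). Eligible individuals are then invited at random from the village lists. On numbers per village it says: "Total number of individuals sampled in each village will be proportionate to the total population of the selected village". The northern hemisphere is deliberately over-represented, with 2000 participants against 1003 in the south.

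**The concern.** A design effect belongs to a particular design. The article ties 1.25 to systematic sampling, but participants are not selected that way. The nearest thing to systematic selection is the blood-metal subset, taken from every tenth participant, which has no bearing on the ECG target.

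The described design is a stratified two-stage cluster sample with unequal selection probabilities. Two features can inflate its variance: similarity of people within a village, and weights needed to undo the northern over-representation. The first is plausible on the study's own reasoning, because exposure is expected to vary with distance, meteorology and topography, and groundwater is sampled village by village. Nothing links 1.25 to either feature.

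At stake is the only precision target in the article. A reader will take 3003 as securing ±2% for the ECG prevalence, and the stated argument does not establish that.

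**Working it through.** **1. Reproduce the plan's figure.** All inputs come from Sample size calculation.

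- Simple random sample: 1.96² × 0.26 × 0.74 / 0.02² = 1848
- Times design effect 1.25: 2310
- Times (1 + 0.30): 3002.7, rounded up to 3003

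The figure reproduces exactly, so 1.25 is a direct multiplier of the total.

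**2. Largest design effect compatible with ±2%.** The article leaves open what 3003 counts. The formula inflates for non-response, which suggests invitees; the sampling text speaks of 3003 participants.

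- All 3003 completed: 3003 / 1848 = 1.63
- 3003 invited, 3003 / 1.3 = 2310 responding: 2310 / 1848 = 1.25

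**3. Clustering.** Deff = 1 + (m − 1) × ICC, where m is the number analysed divided by the number of villages. Margin = 1.96 × √(Deff × 0.26 × 0.74 / n). Village counts and ICC are my assumptions, and villages are treated as equal in size.

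Worked case: 30 villages, 3003 completed, ICC 0.01. Then m = 100.1, Deff = 1 + 99.1 × 0.01 = 1.99, and the margin is 1.96 × √(1.99 × 0.1924 / 3003) = 2.21 points.

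Margins in percentage points, before any weighting:

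| Villages | 3003 completed, ICC 0.005 | 3003 completed, ICC 0.01 | 3003 completed, ICC 0.02 | 2310 responding, ICC 0.005 | 2310 responding, ICC 0.01 | 2310 responding, ICC 0.02 |
|---|---|---|---|---|---|---|
| 10 | 2.48 | 3.13 | 4.15 | 2.62 | 3.25 | 4.23 |
| 20 | 2.07 | 2.48 | 3.13 | 2.24 | 2.62 | 3.24 |
| 30 | 1.92 | 2.21 | 2.71 | 2.10 | 2.37 | 2.84 |
| 60 | 1.75 | 1.92 | 2.21 | 1.95 | 2.10 | 2.37 |

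**4. ICC at which ±2% is just met, clustering only.** (Largest Deff − 1) / (m − 1):

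| Villages | 3003 completed | 2310 responding |
|---|---|---|
| 10 | 0.0021 | 0.0011 |
| 20 | 0.0042 | 0.0022 |
| 30 | 0.0063 | 0.0033 |
| 60 | 0.0127 | 0.0067 |

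**5. North-south allocation.** With f = 2000/3003 the sampled northern share and W the northern population share (not given), the Kish factor is W²/f + (1 − W)²/(1 − f).

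- W = 0.6: 1.02
- W = 0.5: 1.12
- W = 0.4: 1.32

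This multiplies the clustering term. Taking a factor of about 1.12, 30 villages, ICC 0.01 and 3003 completed, Deff rises from 1.99 to 2.24 and the margin from 2.21 to 2.35 points.

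**The case against.** The strongest reply is that the article does not contain the figures needed to show that the target is missed. A reader might infer that 3003 certainly fails to give ±2%. The documents do not support that. With 3003 completed, the margin before weighting is 1.92 points at 30 villages and ICC 0.005, and again 1.92 at 60 villages and ICC 0.01. This objection stands, and the conclusion is worded accordingly.

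A reader might also take the ICC that reproduces Deff 1.25 with 100 people per village, about 0.0025, as the point where the target is lost. It is not: with 3003 analysed in 30 villages the limit is about 0.006, and with 2310 responding it is about 0.003.

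It is tempting to add a large weighting factor for distance zones, about 1.8 if each zone contributes equally and population follows area. The text supports neither assumption. It says a fixed number of villages, not an equal number per zone; village samples follow village population; and a city of more than 0.1 million contains the industrial centre. That factor is not used here.

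Two offsets are fair. Stratifying by hemisphere and zone can lower the variance, and where most villages in a zone are taken, the between-village contribution shrinks. Neither can be quantified from the article, and neither makes 1.25 the right value.

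Finally, ECG prevalence is only one of several outcomes, the objectives are mainly about pollutant levels and associations, and a full protocol may give the village count. This lowers the severity. It does not remove the mismatch, which is between two things the article does state.

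**Conclusion.** The stated basis for 1.25 is wrong for the design described, and nothing in the article reconciles the two sections. Given that design, 3003 is likely to miss ±2% unless the ICC is very small or many villages are drawn. At ICC 0.01 the margin runs from 3.13 down to 1.92 points for 10 to 60 villages if all 3003 are completed, and from 3.25 down to 2.10 if 2310 respond. Weighting for the northern over-representation would widen these by the square root of a factor of about 1.02 to 1.32, for a northern population share of 60% to 40%.

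These sizes rest on assumed village counts, ICC values and population shares, and on equal village sizes. Clustering is the main driver; at equal populations the allocation factor alone (1.12) would fit within 1.25. This should be fixed, but it does not invalidate the study.

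**What to change.** Replace the systematic-sampling justification with a design effect for the described sample: [1 + (m − 1) × ICC] × weighting factor. Use the planned number of villages, a stated ICC range and the actual hemisphere populations. Say whether 3003 counts invited or completed participants. Then restate the achievable margin for 3003 as a range.

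This is a change of wording and needs no extra enrolment. Its cost is a less favourable stated margin. If the village draw is still open and a zone has enough villages, drawing more of them with fewer people in each would recover precision at the same total, at the price of more travel.
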